### 2.7. Data collection and monitoring

All data will be gathered in case report format on printed paper and will be managed in a secure online database. The Mytrial system (http://www.mytrial.co.kr, Bethesdasoft Co., Seoul, Korea) will be used to manage the electronic data. With a user identification and password, only authorized personnel are able to access the database. The data management system will enable automatic editing to record and audit electronic data. The monitoring committee, which does not have any competing interests, will periodically review all of the study documents, including informed consent forms and case report forms containing the data collected.

All study materials will be identified by special codes rather than by participant names to maintain anonymity. Following the release of the results, all data containing participant information will be securely stored for 3 years.

### 2.8. Ethical issues

The institutional review board committee at Kyung Hee University in Seoul, Republic of Korea, has approved this study (KHSIRB-22-074RA). The Declaration of Helsinki will be followed while conducting the study. After receiving a thorough explanation of the study goals, participants’ rights, potential adverse events (AEs), and safety protection, participants will receive consent forms. All participants will have to sign the documents to be enrolled. A separate compensation award will be established in the event of an emergency or serious AE, and patients will receive the best care at each clinic. Additionally, participants will have the option to cancel their participation at any time.

### 2.9. Adverse events

Any mild or significant AE connected with the study will be recorded, along with their frequency and seriousness. After receiving acupuncture therapy, patients will be informed of any potential AEs, such as discomfort, bruising, and bleeding. The principal investigator will evaluate any associations between the AEs and the trial.

### 2.10. Changes to the study protocol

The institutional review board committee will approve any modifications to the protocol before they can be implemented because they may impact the effectiveness of the study, its potential benefits, or the safety of the subjects. Modifications could include changes to the study design, sample size, or procedures.

## 3. Discussion

This study will collect clinical data from 15 multicenter Korean medical clinics that treat FGID as part of an observational study registry. With a machine learning system, we will further determine the best acupoints for treating FGID patients after analyzing the acupoint selection patterns.

Depending on the pattern, multiple acupuncture treatments for the same disease may be suggested by traditional Korean medicine. In a previous study, 69 Korean clinicians were asked to provide diagnoses for hypothetical patients based on the clinical information from a previous study that employed a traditional Korean medicine diagnostic algorithm.^[10]^ The most often used acupoints for individuals with FD were CV12, LI4, LR3, ST36, and PC6 but the choices varied depending on which of the 3 patterns (liver qi depression, spleen-stomach weakness, and food accumulation/phlegm-fluid retention) was present. Ha^[13]^ created a 36-item test for studying functional dyspepsia (STPI-FD) based on the Delphi technique and the opinions of specialists, and from which 6 types of FD were distinguished: spleen and stomach deficiency and cold, spleen deficiency with qi stagnation, liver-stomach disharmony, tangled cold and heat pattern, dampness and heat in the spleen and stomach, and food retention pattern. Depending on the pattern identified, supervised learning will be used to extract important clinical features. For our proposed study, we anticipate that the data collected from the 15 different clinics will reveal various FGID patient patterns and further illustrate the patterns of the chosen acupoint combinations. To identify the optimum acupoints for disorders such as FGID, pattern identification based on supervised learning will be used to extract crucial information from real-world clinical data.

Next, the best acupoints for treating FGID with acupuncture will be predicted using machine learning and the patient results. Individuals respond to acupuncture in different ways.^[18]^ As mentioned above, machine learning can be used to forecast the best acupoints based on patient outcomes. In a previous study, the effectiveness of acupuncture was predicted using a support vector machine for individuals with FD.^[11]^ Gender, disease subtype, and education level were significant predictors of treatment results. Similarly, machine learning will be used to identify those who are more likely to respond to acupuncture, or those who will improve (display minimally clinically significant differences) from baseline following 4 weeks of acupuncture treatment. Data from 80% of the patients with FD will be used to create a predictive model, and the data from the other 20% will be used to validate the model and assess its performance. The performance of supervised machine learning models, such as support vector machine and logistic regression models, will be assessed using accuracy, sensitivity, and specificity analyses. Machine learning can be used to predict the optimal acupoints for each patient and help doctors assess treatment responses.

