### 2.2. Study design

Up to 420 patients with a doctor-diagnosed FGID will participate in this multi-center, prospective observational registry study. This study will be conducted in 15 traditional Korean medical clinics located in the Republic of Korea. All subjects will be recruited from the daily outpatient department of each clinic participating in the study.

First, using various methods of pattern identification, we will investigate the acupoint selection patterns that doctors recommend for patients with FGIDs. Patients with FGIDs will receive a pattern identification questionnaire. Second, we will determine which acupoints are best for treating FGID. A machine learning method will be used to extract the combinations of acupoints to predict the acupuncture responders. Patients included in the study will complete a series of questionnaires a maximum of 3 times throughout their treatment period: at the first appointment (week 0), 2 weeks later (week 2), and 4 weeks later (week 4).

After receiving an explanation of the advantages and disadvantages of participating in the study, the patients will be requested to sign an informed consent form in writing during their initial appointment. They will be assessed for compliance with the inclusion and exclusion criteria in a screening procedure. Eligible subjects will be added to the registry after screening. The patients will receive combined Korean medical treatment for a maximum of 4 weeks, which will include acupuncture treatment and the responses to a series of questionnaires. The detailed study procedure is shown in Figure 1.

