#### 2.4.2. Other co-interventions.

Herbal acupuncture, herbal medicine, cupping therapy, moxibustion, and other treatments will also be provided simultaneously in clinics in addition to traditional acupuncture. Co-interventional data will be considered a covariate when estimating the impact of the treatment.

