### 2.5. Outcomes

The Rome IV criteria will be used first to diagnose FGID. Patients who are assigned to this registry will be required to complete 3 evaluations of the Korean versions of the Nepean Dyspepsia Index,^[14]^ FD-QoL,^[15]^ and IBS-QoL questionnaires.^[16]^ The Nepean dyspepsia index questionnaire includes 15 questions on different dyspepsia symptoms that assess their frequency, seriousness, and subjective perception. Total of 21 questions divided into four areas, including nutrition, vitality, emotions, and social function, in FD-QoL questionnaire reflect how the QoL of FD patients has changed. In all, 34 items on how the QoL of IBS patients has changed are included in the IBS-QoL questionnaire. In addition, the acupuncture expectancy scale will be evaluated at baseline to gauge the general effects of treatment.^[17]^

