### 2.6. Sample size and data analysis

Although sample size calculations are not necessary for observational registry studies, we have determined that 420 individuals are needed, considering the volume of business at the outpatient clinics taking part in this study.

Each outcome measure will be compared to the clinical outcome between the baseline and termination, and the clinical outcome will be a dependent variable. Combinations of the applied acupoints will act as independent factors to predict the most effective acupoints for the acupuncture treatment. To improve the effectiveness of acupuncture treatments for FGID patients, the properties of the acupoints will be extracted using machine learning algorithms, such as support vector machine and logistic regression models.

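### The responder label discards much of the information in the questionnaire scores, and, as a separate point, baseline score is not named as a predictor or covariate although response is a change from baseline

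*Protocol article*

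**What the plan says.** Section 2.2 gives the aim of the learning step: "A machine learning method will be used to extract the combinations of acupoints to predict the acupuncture responders". The Discussion describes the target as "those who will improve (display minimally clinically significant differences) from baseline following 4 weeks of acupuncture treatment". It names supervised models "such as support vector machine and logistic regression models, will be assessed using accuracy, sensitivity, and specificity analyses", measures that need a binary outcome.

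The data are richer than that. Under section 2.5 patients "will be required to complete 3 evaluations of the Korean versions of the Nepean Dyspepsia Index", and of the FD-QoL and IBS-QoL as well. These have 15, 21 and 34 questions. Section 2.2 places the assessments at weeks 0, 2 and 4.

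On the right-hand side of the model, section 2.6 says: "Combinations of the applied acupoints will act as independent factors to predict the most effective acupoints for the acupuncture treatment". Section 2.4.2 adds: "Co-interventional data will be considered a covariate when estimating the impact of the treatment". The baseline score is named in neither place. According to the Discussion, the model is built on 80% of the FD patients and validated on the other 20%.

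**The concern.** There are two separate issues.

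**Loss of information.** A yes/no label treats a patient who just misses the threshold like one who deteriorated, and one who just reaches it like one who recovered. Acupoint effects are then estimated less precisely than the collected scores allow, in a sample whose size was set by clinic volume and not by a precision target.

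**Baseline severity.** A change from baseline usually correlates with the baseline value: high scores tend to fall and low scores tend to rise, whatever the treatment. Doctors choose acupoints by pattern and may add points for additional symptoms, without limit on number (section 2.4.1). If severity influences that choice, a model without the baseline score can credit an acupoint with improvement that belongs to severity. The Discussion expects the models to point to optimal acupoints for individual patients, so such an artefact could reach practice.

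**Working it through.** The plan has no figure of its own to reproduce. The 420 in section 2.6 rests on clinic volume, and the article gives no SD, responder share, baseline-to-follow-up correlation or acupoint effect. These are assumptions below, shown as ranges.

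**1. Information kept by the label.** For a shift in a normal outcome, with responder share p and cut at z, the large-sample efficiency of the binary against the continuous analysis is φ(z)² / [p(1−p)]. For a logistic-shaped outcome, against a linear model, it is p(1−p)·π²/3.

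| Responder share | Normal: kept | Normal: lost | Logistic: kept | Logistic: lost |
|---|---|---|---|---|
| 50% | 0.399²/0.25 = 63.7% | 36.3% | 0.25 × 3.290 = 82.2% | 17.8% |
| 40% | 62.2% | 37.8% | 79.0% | 21.0% |
| 30% | 0.348²/0.21 = 57.6% | 42.4% | 0.21 × 3.290 = 69.1% | 30.9% |
| 20% | 49.0% | 51.0% | 52.6% | 47.4% |

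Under normality 36.3% is the smallest possible loss. The measure concerns the precision of an effect estimate, not classifier accuracy.

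**2. The base it applies to.** Up to 420 patients with FD or irritable bowel syndrome (IBS) enter, but the model trains on 80% of those with FD. If all 420 had FD, that is 0.8 × 420 = 336, and 336 × 0.637 ≈ 214 at a 50% share under normality. If half had FD (an assumption), it is 0.8 × 210 = 168, and 168 × 0.637 ≈ 107.

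**3. Link between baseline and response.** Let ρ be the correlation of baseline and follow-up, and k the follow-up SD divided by the baseline SD. Then r = corr(baseline, change) = (1 − ρk) / √(1 + k² − 2ρk). With bivariate normality, a cut at the median change and no acupoint effect, the response rate is 1/2 ± arcsin(r)/π above and below the median baseline.

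| k | ρ | r | Above vs below median |
|---|---|---|---|
| 1.0 | 0.3 | 0.59 | 70% vs 30% |
| 1.0 | 0.5 | 0.50 | 67% vs 33% |
| 1.0 | 0.7 | 0.39 | 63% vs 37% |
| 1.2 | 0.7 | 0.18 | 56% vs 44% |
| 1.2 | 0.8 | 0.055 | 52% vs 48% |

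The share of variation in change explained by baseline is r². For ρ from 0.3 to 0.8 it runs from 35% down to 10% at k = 1.0, from 50% to 36% at k = 0.8, and from 24% to 0.3% at k = 1.2. An acupoint used in half the patients, with effect d in SDs of change, explains 0.25d²/(1 + 0.25d²): 2.2% at d = 0.3 and 5.9% at d = 0.5.

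**4. When this distorts an acupoint comparison.** The slope of change on baseline is 1 − ρk. If users of a point differ from non-users by δ baseline SDs, the spurious difference in mean change is δ(1 − ρk) baseline SDs. Take δ = 0.2 (assumed), ρ = 0.5 and k = 1. The result is 0.2 × 0.5 = 0.10, and the SD of change is then also 1, so this is 0.10 SD of change. At a median cut that is about 0.10 × 0.399 ≈ 4 percentage points in response. With δ = 0 it is nil.

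**The case against.** The strongest reply is that predicting responders is the stated aim, so classification answers the question asked. Section 2.6 is also wider than the Discussion: "Each outcome measure will be compared to the clinical outcome between the baseline and termination, and the clinical outcome will be a dependent variable", without saying that this variable is binary. Its algorithms are only examples ("such as support vector machine and logistic regression models"), and a support vector method can also be used for regression. The article is condensed, and the full plan may set the threshold and a longer covariate list. The Discussion itself mentions extracting clinical features by pattern.

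Much of this stands. A direct comparison of scores is not ruled out, and the absence of a complete covariate list is not counted here as an error. But the definition of the target and the performance measures are stated choices. The probability of response can also be obtained from a continuous model, so the aim does not require the label as the training outcome.

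Several stronger readings are tempting and not supported:

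- *The cut makes baseline severity the main driver of response.* The link comes from using unadjusted change; a continuous unadjusted change has it too. Its strength ranges from almost none to about half of the variation.
- *Every acupoint comparison is distorted.* That needs acupoint choice to depend on severity. Section 2.4.1 makes this possible for some points and shows it for none.
- *Mild patients cannot respond.* That needs an absolute threshold and patients who start below it. The article gives neither the form of the threshold nor any score distribution.
- *Over a third of the information in 420 patients is lost.* The fraction needs a roughly normal change, and 420 is not the training set.

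**Conclusion.** The concern holds as two separate, moderate points.

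The yes/no target costs about 36% or more of the information on acupoint effects if the change is roughly normal. It costs less if the tails are heavier: about 18% at a 50% responder share and 31% at 30% for a logistic shape. The cost falls on the learning step, whose training set is at most 336 patients and smaller by however many have IBS only.

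The label is also a change from baseline, while the baseline score is not among the named predictors and covariates. Under equal SDs and correlations of 0.3 to 0.7, response differs clearly by baseline severity, and baseline explains more of the change than a single acupoint effect of 0.3 to 0.5 SD would. If the follow-up SD exceeds the baseline SD, the dependence can be slight. Bias in an acupoint result follows only where the choice of that point varies with severity, which the article makes plausible but does not establish. This is a choice worth improving; it does not invalidate the registry.

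**What to change.** Make the main model a regression of the week-4 score, on its continuous scale, on acupoint combinations with the baseline score and co-interventions as covariates. Penalised linear regression or support vector regression would suit the learning step. Derive each patient's probability of reaching the minimal important difference from that model. Keep the responder classification, with accuracy, sensitivity and specificity in the 20% validation set, as a secondary report.

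The cost is a wording change in the analysis plan, slightly more analysis work and a headline result that is less direct than a responder rate. Baseline and week-4 scores are already collected, so no new data or visits are needed.

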#### 2.3.1. Inclusion criteria.

Patients diagnosed with FD (either epigastric pain syndrome or postprandial distress syndrome) or IBS via the Rome Ⅳ Criteria, who can consistently visit a clinic for treatment, and who voluntarily agree to participate will be included in the study.

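### The prediction model is validated on one 20% hold-out of at most 84 patients with FD, so its performance will be imprecise and, if patients are split within clinics, may be mildly optimistic for a new clinic

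*Protocol article*

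**What the plan says.** The validation design is in section 3 (Discussion) of the protocol article. On model building it says "Data from 80% of the patients with FD will be used to create a predictive model", and on testing it says "the data from the other 20% will be used to validate the model and assess its performance". The support vector machine and logistic regression models "will be assessed using accuracy, sensitivity, and specificity analyses".

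Four other statements set the scale:

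- Section 2.2: "Up to 420 patients with a doctor-diagnosed FGID will participate in this multi-center, prospective observational registry study".
- Section 2.2: "This study will be conducted in 15 traditional Korean medical clinics located in the Republic of Korea".
- Section 2.3.1 admits "Patients diagnosed with FD (either epigastric pain syndrome or postprandial distress syndrome) or IBS", so the FD subset used for the model may be well below the registry total.
- Section 2.6 gives the basis of the total: "we have determined that 420 individuals are needed, considering the volume of business at the outpatient clinics taking part in this study". No precision target for the model is stated.

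Section 2.6 also names the predictors: "Combinations of the applied acupoints will act as independent factors to predict the most effective acupoints for the acupuncture treatment". Under sections 2.4 and 2.4.1 the treating doctor decides the treatment, pattern identification guides the choice of acupoints, and the number of points is not limited.

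The article names the patient as the unit of the split. It does not say whether the split is random, stratified or by clinic.

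**The concern.** Two separate matters arise from the one design choice.

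The first is precision. A single hold-out lets only one patient in five contribute to the performance estimate. Sensitivity and specificity each use only part of that fifth. The answer also depends on which patients happen to fall in it. No assumption about clinics is needed for this.

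The second is what the estimate refers to. If patients are split without regard to clinic, each clinic supplies both training and test patients. Where doctors in a clinic share acupoint preferences, and responder rates differ between clinics, the acupoint pattern can partly stand in for the clinic. The model is then rewarded for recognising a clinic that it has already seen, and that reward would not carry over to a clinic outside the registry.

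At stake is how far the article's closing aim, predicting optimal acupoints for individual patients and helping doctors judge response, can rest on the reported performance.

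**Working it through.** **Inputs from the article.** Maximum enrolment 420 (2.2, 2.6); 15 clinics (2.2); test share 20% of patients with FD (3).

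**Inputs assumed, because the article does not give them.** FD share 50% to 100%; loss 0% or 15%; responder share 30% or 50%; equal clinic size, 420/15 = 28; intraclass correlation (ICC) of response between clinics 0 to 0.20; spread of clinic acupoint preference, SD 0 to 2 on the logit scale.

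The 420 has no statistical derivation, so there is no planned figure to reproduce.

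**Step 1: size of the hold-out.** n = 0.20 × 420 × FD share × (1 − loss).

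- All FD, no loss: 0.20 × 420 = 84 (336 left for training)
- 75% FD, no loss: 0.20 × 315 = 63
- 50% FD, no loss: 0.20 × 210 = 42
- 50% FD, 15% loss: 0.20 × 178.5 = 35.7, about 36

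**Step 2: precision.** Wilson 95% interval with p = x/n and z = 1.96: centre (p + z²/2n)/(1 + z²/n), half-width z·√(p(1−p)/n + z²/4n²)/(1 + z²/n).

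For 59/84, p = 0.702. The centre is (0.7024 + 0.0229)/1.0457 = 0.694 and the half-width is 1.96 × 0.0512/1.0457 = 0.096. The interval is 59.8% to 79.0%. In the same way:

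| Measure | Count | 95% CI |
|---|---|---|
| Accuracy, n = 84 | 59/84 | 59.8% to 79.0% |
| Accuracy, n = 63 | 44/63 | 57.6% to 79.8% |
| Accuracy, n = 42 | 29/42 | 54.0% to 80.9% |
| Accuracy, n = 36 | 25/36 | 53.1% to 82.0% |
| Sensitivity, n = 84, 50% responders | 29/42 | 54.0% to 80.9% |
| Sensitivity, n = 84, 30% responders | 18/25 | 52.4% to 85.7% |
| Sensitivity, n = 42, 50% responders | 15/21 | 50.0% to 86.2% |

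With 50% responders, specificity has the same intervals as sensitivity.

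**Step 3: would clinics be shared between the sets?** Under a random split by patient, the chance that a given clinic of 28 has no test patient is C(392,84)/C(420,84) = 0.0015, and 84/15 = 5.6 test patients are expected per clinic. If half have FD (14 per clinic, 42 tested), the chance is C(196,42)/C(210,42) = 0.039. Nearly every clinic would be in both sets.

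**Step 4: possible optimism.** Simulated registries of 15 × 28 patients had ten binary acupoints with no true effect and an average responder rate of 50%. A ridge logistic model was tested on a random 20% of patients and, separately, on three whole clinics held out (600 runs per setting). Mean accuracy:

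| ICC | Preference SD | Split by patient | Clinics held out | Gap (points) |
|---|---|---|---|---|
| 0 | 1 | 50.2% | 50.2% | 0.0 |
| 0 | 2 | 50.1% | 50.1% | 0.0 |
| 0.05 | 1 | 51.2% | 50.0% | 1.2 |
| 0.05 | 2 | 52.1% | 49.8% | 2.3 |
| 0.10 | 1 | 52.3% | 50.6% | 1.7 |
| 0.10 | 2 | 53.7% | 50.2% | 3.5 |
| 0.20 | 1 | 53.9% | 50.3% | 3.6 |
| 0.20 | 2 | 56.2% | 50.2% | 6.0 |

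Not all of the gap comes through the acupoints. At ICC 0.20 with no clinic preference at all (SD 0), the figures were 52.4% and 49.9%, a gap of 2.5 points, because the intercept learns the average responder rate of these particular clinics. A comparison model without acupoints would show that part.

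**Step 5: precision if every patient is predicted once, out of fold.** For 70% accuracy, 294/420 gives 65.5% to 74.2% and 147/210 gives 63.5% to 75.8%. These are best cases, since they ignore clustering and dependence between folds.

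**The case against.** The strongest reply is that much of the clinic argument is inference. The article never says that the split is random or pooled over clinics. Holding out 3 of the 15 clinics would also make a 20% test set, and the mechanics of a split may properly sit in a fuller document. Section 2.4.1 ties acupoint choice to pattern identification, and the Discussion reports that choices varied by pattern, so clinic habit is plausible but not documented. No ICC is given. The article makes no explicit claim of validated performance in a new clinic, and for further patients of the same clinics a split by patient answers the right question. All of this stands, and it makes the optimism conditional.

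Three stronger readings may tempt a reader, and the documents do not support them.

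- That the predictive claim would rest on leaked clinic information. The simulated gap is nil at ICC 0, 1 to 2 points at ICC 0.05 and 4 to 6 points at ICC 0.20. Each is smaller than the half-width of about 10 points at n = 84.
- That the hold-out cannot tell a useful model from a useless one. This is too absolute: 59.8% to 79.0% excludes 50%.
- That accuracy would be reported alone, so that a rule calling everyone a responder could pass unnoticed. The article also names sensitivity and specificity, and such a rule would have a specificity of zero.

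A fair practical objection is that leave-one-clinic-out folds hold about 28 patients at most on average, too few for stable sensitivity or specificity in each clinic. That is a reason to pool the out-of-fold predictions, not to keep the single split.

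None of this touches the precision point, which follows from the stated split and the stated maximum enrolment.

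**Conclusion.** The point holds in two parts of unequal strength.

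The imprecision is firm. The hold-out is at most 84 patients, and that ceiling is reached only if every enrolled patient has FD and is evaluable. Accuracy near 70% would be known to about ±10 points at n = 84 and about ±13 points at n = 42, and sensitivity and specificity less well. The smaller hold-outs depend on an assumed FD share and loss, and the intervals for sensitivity and specificity on an assumed responder share.

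The optimism is possible, not shown. It requires a split by patient (the natural reading, but not stated), responder rates that differ between clinics and, for the larger values, acupoint choices that differ by clinic. Under the assumptions above it ranges from 0 to about 6 accuracy points. The article therefore does not support a statement that reported performance will be optimistic, only that it may be mildly so for a new clinic.

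The change is worth making, because a more efficient design is available with the data already planned and it settles both parts.

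**What to change.** Replace the single 80/20 split with leave-one-clinic-out (internal-external) cross-validation over the 15 clinics:

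- Do all tuning and feature selection inside each training fold.
- Pool the out-of-fold predictions, and do not report single clinics separately.
- Report accuracy, sensitivity, specificity and AUC with confidence intervals that allow for clustering by clinic.
- Set these beside the same model without acupoints, so that what the acupoints add is visible.
- Fit the final model on all patients with FD.

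If a split by clinic is already intended, the text should say so; the precision argument for cross-validation would remain.

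The cost is slightly more analysis work, with no change to recruitment, visits or data collection. Performance figures may look a little less favourable.

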#### 2.4.1. Acupuncture treatment.

Based on the top 10 frequently used acupoints according to previous systematic reviews, examples of acupoints (e.g., CV12, ST25, ST36, CV10, LR3, BL20, PC6, GV7, BL21, and SP6) will be shown in the case report form. Pattern identification will be used to choose the acupoints, and more acupoints will be permitted based on the patient additional symptoms. There will be no restrictions on the number of acupoints used for treatment. Korean medical experts with at least 5 years of clinical practice will deliver all acupuncture treatments.

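### Accuracy, sensitivity and specificity for classifying responders do not show whether acupoints contribute, so they cannot support a conclusion about the best acupoints

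*Protocol article*

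**What the plan says.** The aim, given in sections 1, 2.2 and 3 of the Protocol article, is to find the best acupoints for functional gastrointestinal disorders. The parts of the plan that bear on this are as follows.

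- **Target.** Section 3: "machine learning will be used to identify those who are more likely to respond to acupuncture". A responder is a patient who improves from baseline by a minimal clinically important amount after 4 weeks. Section 2.2 agrees: "A machine learning method will be used to extract the combinations of acupoints to predict the acupuncture responders".
- **Inputs.** Section 2.6: "Combinations of the applied acupoints will act as independent factors to predict the most effective acupoints for the acupuncture treatment". Section 3 adds: "Depending on the pattern identified, supervised learning will be used to extract important clinical features".
- **Performance.** Models are built on 80% of the functional dyspepsia (FD) patients and validated on the other 20%. Performance of the support vector machine and logistic models "will be assessed using accuracy, sensitivity, and specificity analyses".
- **Conclusion in view.** Section 3: "Machine learning can be used to predict the optimal acupoints for each patient and help doctors assess treatment responses".
- **How acupoints are chosen.** Section 2.4.1: "Pattern identification will be used to choose the acupoints, and more acupoints will be permitted based on the patient additional symptoms". Every patient receives acupuncture (section 2.4).
- **Adjustment.** Section 2.4.2 names co-interventions as a covariate. No other covariate is named.

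**The concern.** The performance measures answer one question and the conclusion answers another. Accuracy, sensitivity and specificity say how often the model sorts responders from non-responders. They do not say how much of that sorting comes from the acupoints, nor whether a different set would have served a given patient better.

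The gap matters here because acupoints are not assigned independently of prognosis. They follow pattern and symptoms, which may themselves predict improvement. An acupoint can then act as a marker of the kind of patient who receives it and carry predictive information without having any effect. Co-intervention adjustment alone does not remove this. At stake is the study's second aim: a respectable hold-out accuracy could be published as evidence for particular acupoints when it reflects only who was given them.

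**Working it through.** **The plan's own figure.** The only figure is the sample size of 420, set in section 2.6 from clinic volume without alpha, power or effect size. There is nothing to reproduce. The check is whether the stated measures can look good when acupoints do nothing.

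**Inputs from the document.** 420 patients with FD or irritable bowel syndrome (IBS) together; an 80/20 split applied to FD patients; logistic regression among the named models; ten example acupoints (section 2.4.1); choice of acupoints by pattern and symptoms.

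**Assumptions, not in the document.**
- The number of FD patients is not given. Two cases: all 420 have FD (336 training, 84 test), or half do (210: 168 training, 42 test).
- Ten yes/no acupoints, each with a true effect of exactly zero.
- Response depends only on severity and sex: logit P(response) = b × severity + c × (sex − 0.5), with severity in SD units, b = 1.0, 1.5 or 2.0 and c = 0.8 or 1.0. The responder rate is about 50%.
- Acupoint choice: logit P(point used) = ±g × severity, with five points favoured and five disfavoured as severity rises. g = 0 is choice unrelated to severity; g = 0.5 and 1.0 are choice by indication.
- Ridge-penalised logistic regression, 400 repeats per setting.

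**Result 1: acupoints as the only inputs (mean held-out accuracy).**

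| Acupoint choice | 420 FD patients | 210 FD patients |
|---|---|---|
| Unrelated to severity (g = 0) | 0.50 | 0.49 to 0.50 |
| g = 0.5 | 0.58 to 0.64 | 0.57 to 0.62 |
| g = 1.0 | 0.63 to 0.71 | 0.61 to 0.69 |

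Sensitivity and specificity moved with accuracy. At 420 patients, b = 2.0 and g = 1.0, they were 0.703 and 0.711. All of the gain over 0.50 is confounding, because the points were inert.

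**Result 2: severity and sex also in the model (mean held-out accuracy).**

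| FD patients | With acupoints | Without acupoints | Gain from acupoints |
|---|---|---|---|
| 420 | 0.67 to 0.77 | 0.68 to 0.78 | −0.008 to −0.014 |
| 210 | 0.65 to 0.77 | 0.68 to 0.78 | −0.014 to −0.027 |

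The model with acupoints looks respectable when read alone. Only the difference between the two models shows that acupoints add nothing.

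**Precision of one hold-out.** The 95% half-width for an accuracy p on n test patients is 1.96 × √(p(1 − p)/n). At p = 0.70 it is 1.96 × √(0.21/84) = 0.098 for n = 84, and 1.96 × √(0.21/42) = 0.139 for n = 42. A single 20% hold-out is a weak basis for estimating a small increment.

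**The case against.** The strongest case against is that performance assessment and acupoint identification are separate steps. Section 2.6 says acupoint properties will be extracted, the article sets no pass mark, and nowhere does it say that good accuracy proves which points are best. The sentence on optimal acupoints describes what machine learning can do and is not an analysis rule. Importance measures, kernels and reference models may be in a fuller plan. Much of this is fair. What remains is that the article fixes these measures and this conclusion side by side, and that acupoint weights taken without adjustment for pattern and severity would be confounded in the same way.

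Several stronger readings are tempting but are not supported.

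- A reader might infer that severity or sex will drive the model. Sections 2.2 and 2.6 name acupoint combinations as the inputs. "Gender, disease subtype, and education level were significant predictors of treatment results" reports an earlier study, and the clinical features in section 3 allow patient inputs without specifying them. Result 1 does not need them.
- A reader might infer that accuracy would look the same whenever acupoints are inert. It would not: with acupoints as the only inputs and choice unrelated to prognosis, it falls to chance.
- A reader might infer that every patient would receive the same ranking of acupoints. That holds for additive models. The kernel of the support vector machine is not stated, and a non-linear one can carry interactions.
- A reader might infer that majority-class guessing would pass unnoticed. It would give a sensitivity or specificity of zero, and both are reported.

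**Conclusion.** The point holds in a limited form. The three measures assess classification of responders and cannot by themselves support a statement about best or per-patient acupoints, because acupoints are chosen by indication and adjustment is named only for co-interventions.

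Under the stated assumptions, inert acupoints used alone reach a mean held-out accuracy of 0.58 to 0.71 with 420 FD patients and 0.57 to 0.69 with 210. With patient features in the model, the true gain from acupoints is nil to slightly negative while the full model still shows 0.65 to 0.77. The sizes depend on assumed effects, an assumed responder rate and an assumed number of FD patients. The direction requires only that acupoint choice is related to prognosis. The documents make this plausible but do not measure it. The article does not show that its conclusions will be wrong, only that the stated measures could not reveal it if they were.

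**What to change.** 1. Fit a reference model without acupoints on data already collected: baseline symptom or quality-of-life score, diagnosis or subtype, STPI-FD pattern, acupuncture expectancy, co-interventions and clinic.
2. Add acupoints and report the change in AUC and accuracy with an interval. Estimate it by repeated cross-validation over all FD patients, not from one 20% hold-out.
3. Report the change as an estimate. Do not declare acupoints non-predictive when the interval includes zero. In a simulation of 600 replicates with ten acupoints, three of them truly active at an odds ratio of 2.0 each, the 95% interval for the AUC gain on the single hold-out excluded zero in only about 11% of runs at 420 patients and 4% at 210. At an odds ratio of 2.7 it did so in 25 to 32% and 11%.
4. Word the conclusion as acupoints associated with improvement given baseline characteristics. Make per-patient or per-pattern statements only if acupoint-by-pattern terms are modelled and improve prediction.

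The cost is some extra analysis, with no new data and no change to care. The increment will be imprecise and may look less favourable than raw accuracy. It also remains an association, since the reference model adjusts only for what was measured.
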